## Abstract

**Purpose:**

Postherpetic neuralgia (PHN) is a type of refractory neuropathic pain that causes significant suffering, disability, economic loss, and medical burden. In this study, we aim to evaluate the efficacy and safety of interferon (IFN)-α1b injection into the intervertebral foramen of patients with PHN.

**Patients and methods:**

This is a study protocol for a randomized, double-blind placebo-controlled multicenter clinical trial. A total of 200 participants with PHN from 11 hospitals will be recruited and randomly assigned to the treatment group administered with IFN-α1b and control group treated with placebo in a 1:1 ratio. Both groups will also receive oral pregabalin 150 mg twice daily and lidocaine injection into the intervertebral foramen as conventional therapy. This trial will involve a screening period, a 2-week intervention, and a 3-month follow-up. The primary outcomes will include the visual analog scale score and duration of pain relief. The secondary outcomes will include the 36-item short-form, dosage and duration of painkillers taken, viral load of varicella-zoster virus DNA, humoral cytokine level, and dosage and frequency of rescue medication. All adverse events and severe adverse events will be assessed during the study.

**Conclusion:**

This study is expected to provide evidence for the efficacy and safety of IFN-α1b injection into the intervertebral foramen in patients with PHN.

**Clinical trial registration:**

https://www.chictr.org.cn/indexEN.html, identifier ChiCTR240008996.

## Introduction

1

Postherpetic neuralgia (PHN) is the most frequent chronic complication of herpes zoster (HZ), which results from the reactivation of latent varicella-zoster virus (VZV) within the dorsal root ganglia (DRG) (1, 2). PHN is defined as pain lasting >90 days after the onset of an acute HZ rash. In China, approximately one-third of individuals with HZ develop PHN (3). Patients with PHN often report different types of pain and characteristic sensory perturbations (such as tingling or pricking sensation, pain on light touch, pain on cold/heat sensation, electric shock-like pain, numbness, and pain on slight pressure). PHN is a highly burdensome condition for patients, families, and society and has major implications for public health (4).

No disease-modifying therapy is currently available for PHN, and treatment is focused on symptom control. Gabapentin, pregabalin, and tricyclic antidepressants (TCAs) are recommended as first-line oral drugs for treating PHN (5). However, clinical studies have found that gabapentin and pregabalin cause adverse reactions including dizziness, drowsiness, dry mouth, weight gain, and edema (6). The use of TCAs increases the incidence of cardiovascular disease. Topical therapies, such as lidocaine and capsaicin patches, alleviate pain only in patients without skin lesions on painful sites (7, 8). Consequently, there is a dire need for novel therapies that are effective and have good tolerability, to mitigate the impact of PHN on patients’ lives.

The activation and replication of VZV are key mechanisms in the occurrence of PHN. VZV detection rate in patients with PHN can reach 3/4 within 2–6 months after disease onset, and can still be detected up to 2 years later (9). Therefore, we inferred that VZV may directly cause severe and irreversible damage to the nervous system during the pathogenesis of PHN, indirectly promoting the formation of PHN.

Interferons (IFNs), a family of cytokines produced by immune cells after a viral infection, bind to cell surface receptors to produce various antiviral proteins, which act on multiple stages of virus replication to achieve multi-target inhibition of virus replication (10). IFN-α1b is a new type of drug with independent intellectual property rights in China having antiviral, antitumor, and immune regulation functions (11, 12). However, evidence-based multicenter clinical research on the efficacy and safety of IFN-α1b injection into the foramen is still lacking. This study will adopt a multicenter, randomized, double-blind, placebo-controlled experimental design to test the efficacy and safety of IFN-α1b injection into the intervertebral foramen, for treating PHN.

## Methods and analysis

2

### Study design and setting

2.1

This study will be a randomized, double-blind, placebo-controlled multicenter clinical trial designed to evaluate the efficacy and safety of IFN-α1b injection into the foramen in patients with PHN. This study will be performed at 11 hospitals in China: China-Japan Friendship Hospital, First Affiliated Hospital of Chongqing Medical University, CR & WISCO General Hospital, Second Affiliated Hospital of Guangzhou Medical University, First Hospital of Lanzhou University, First Affiliated Hospital of Xiamen University, Affiliated Hospital of Xuzhou Medical University, Yanbian University Hospital, Nanjing Drum Tower Hospital, Jilin Provincial People’s Hospital, and Gansu Provincial Hospital. Two-hundred participants who meet the inclusion criteria but not the exclusion criteria will be randomly divided into treatment and control groups in a 1:1 ratio. The study will include a baseline period, a 2-week treatment, and a 3-month follow-up after enrollment. Individual researchers will screen subjects who meet the inclusion criteria. Subjects who do not meet the exclusion criteria will be included in this study. Collection of baseline information will be completed through case report form (CRF) during the baseline period. The experimental flowchart is shown in Figure 1 by Figdraw. The schedules for enrollment, intervention, and assessment are listed in Table 1.

**Figure 1 fig1:**
[figure not shown]
Flowchart of the experimental: efficacy and safety of ultrasound-guided injection of interferon-alpha1b (IFN-alpha1b) into foramen of patients with postherpetic neuralgia.

**Table 1 tab1:** Schedule of enrolment, treatments, and assessments.

Procedure	Screening period	Treatment period		Follow-up period		
	Visit 1	Visit 2	Visit 3	Visit 4	Visit 5	Visit 6
	Day −3 to 0	Day 7 (After 2 treatments)	Day 14 (After 4 treatments)	Day 30 after treatment	Day 60 after treatment	Day 90 after treatment
Enrolment						
Informed consent	•					
Demographic information	•					
Vital sign	•	•	•	•	•	•
Physical examination	•	•	•	•	•	•
Imaging test	•					
ECG	•					
Laboratory test	•		•			
Randomization	•					
Intervention						
Treatment group		Inject interferon into intervertebral foramen 2 times per week				
Control group		placebo interferon into intervertebral foramen 2 times per week				
Assessment						
VAS	•	•	•	•	•	•
Duration of pain relief	•	•	•	•	•	•
SF-36	•	•	•	•	•	•
Virus load of VZV DNA	•		•			
humoral cytokine level	•		•			
Drug consumption	•	•	•	•	•	•
Adverse events		•	•	•	•	•

ECG, electrocardiogram; VAS, visual analogue scale; SF-36, 36-item short-form; VZV, varicella-zoster virus. Indicate completion or inclusion of the content.

### Sample size

2.2

A preliminary study with a small sample size and ≥ 25% reduction in VAS after one treatment as the primary outcome showed that the response rate was 46% in the treatment group and 23% in the control group. With *α* = 0.05 (bilateral) and power = 0.90, PASS17 software suggested that at least 85 subjects should be included in each group. Assuming a loss to follow-up rate of 15%, the adjusted sample size should be 100.

### Inclusion criteria

2.3

Participants who meet all the following requirements will be enrolled:

Aged 50–80 years.Pain lasting for >3 months after the onset of rash.VAS score ≥ 4 during the screening period.Only involving the cervical, thoracic, or lumbar spinal nerves.Voluntarily willing to participate and provide written informed consent.

### Exclusion criteria

2.4

Participants who meet one of the following requirements will be excluded:

Head, face, and special area affected by HZ.Puncture site affected by HZ.Presence of coagulation disorders.Severe heart and lung dysfunction, including a history of angina, myocardial infarction, or other serious cardiovascular diseases.Long-term use of glucocorticoids or immunosuppressants.Presence or history of autoimmune diseases.Presence of liver or kidney disease: alanine transaminase (ALT) and aspartate transaminase (AST) levels exceed the upper limit of normal values by more than five times or a creatinine clearance rate < 60 mL/min.Allergy to IFN.Presence of contraindications to IFN, including history of epilepsy or other central nervous system dysfunction, and abnormalities in the hematopoietic system (platelets <30 × 10^9^/L or neutrophils <0.5 × 10^9^/L).Intake of antiviral drugs, such as acyclovir and bromouridines, within 1 week before screening period.Other disqualifications as determined by researchers.

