### Drop-out criteria

2.5

During this trial, subjects experiencing the following conditions will be considered as dropout cases, and the reason and date of dropout will be recorded in a case report form.

Self-administration of drugs that affects the trial.Occurrence of adverse events (AEs) or severe adverse events (SAEs), which makes it inadvisable to continue considering the subjects’ interests.Abnormal blood routine changes (platelets <30 × 10^9^/L, neutrophil count <0.5 × 10^9^/L) during the administration of intervertebral foramen injections, leading the researchers to determine that further participation would pose a greater risk than benefit to the subjects.A participant requests to withdraw consent.A participant is lost to follow-up.The researchers consider that further participation will be inappropriate.

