## Intervention

3

Participants will receive four injections into the foramen in 2 weeks according to group allocation. The injection drugs for the treatment group include 30 μg (1 mL) IFN-α1b, 50 mg lidocaine, and 2 mL physiological saline, while the control group will be treated with 30 μg placebo (1 mL), 50 mg lidocaine, and 2 mL physiological saline. The placebo is a solvent for IFN, and its packaging and appearance are consistent with those of the experimental drug. IFN-α1b injection and placebo are both produced by Sanyuan Gene Pharmaceutical Co., Ltd., Beijing, China. Every subject will be administered 150 mg of pregabalin twice daily as part of conventional therapy.

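### Section 2.5 provides for withdrawal on low blood counts during the injections, but no count is scheduled until after the fourth one, and the Section 2.4 entry limits leave no margin

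*Protocol article*

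**What the plan says.** Four parts of the protocol article bear on this point.

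- **Entry (Section 2.4).** Among the contraindications to interferon, patients are excluded for "abnormalities in the hematopoietic system (platelets <30 × 10^9^/L or neutrophils <0.5 × 10^9^/L"). The list also excludes "Presence of coagulation disorders" and allows "Other disqualifications as determined by researchers".
- **Drop-out (Section 2.5).** One ground for dropping out is "Abnormal blood routine changes (platelets <30 × 10^9^/L, neutrophil count <0.5 × 10^9^/L) during the administration of intervertebral foramen injections". A low count is not enough by itself; the criterion adds a condition about its consequence, namely "leading the researchers to determine that further participation would pose a greater risk than benefit to the subjects".
- **Treatment (Section 3).** "Participants will receive four injections into the foramen in 2 weeks according to group allocation".
- **Testing (Table 1, Sections 6 and 8).** Table 1 marks the laboratory test at Visit 1 (Day −3 to 0) and at Visit 3, "Day 14 (After 4 treatments"). The cell for Visit 2, "Day 7 (After 2 treatments"), is empty. Section 6 places hematology before and after treatment, and Section 8 compares laboratory results at screening with those at the end of the intervention. Section 6 also lists a fall in granulocytes and a fall in platelets among the possible treatment-related reactions.

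**The concern.** A withdrawal rule that applies during the injections needs a result during the injections. On the stated schedule there is none: the first count after baseline comes once the last dose has been given. The rule can then act only if someone orders a test outside the schedule.

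A generous entry limit could make up for this by ensuring that patients start well above the level of concern. Here the entry limit is the withdrawal limit, so it gives no such protection. A patient just above it could receive four foraminal injections of a drug that the protocol says may lower these counts, and a fall below the limit might not be seen until the course is over. What is at stake is the safety of a small number of patients, not the efficacy comparison.

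**Working it through.** The plan states no figure that needs reproducing here. The check compares the limits and counts the scheduled tests.

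**1. Margin between entry and withdrawal limits** (Sections 2.4 and 2.5, units 10^9/L)

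- Platelets: 30 − 30 = 0
- Neutrophils: 0.5 − 0.5 = 0

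Both rules use a strict less-than. A patient at exactly 30 or 0.5 is eligible on this criterion and is not yet at a level that Section 2.5 flags, but any fall from there would be.

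**2. Scheduled counts against injections** (Table 1 and Section 3)

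| Time | Injections given by then | Laboratory test marked |
|---|---|---|
| Visit 1, Day −3 to 0 | 0 | yes |
| Visit 2, Day 7 | 2 | no |
| Visit 3, Day 14 | 4 | yes |

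Scheduled counts after the first injection and before the fourth: 0. All 4 of 4 injections rest on the screening count.

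The empty Day 7 cell is unlikely to be an artefact of the text extraction. The viral load and cytokine rows of Table 1 show the same pattern, and Section 5.2.2 confirms it for those samples: screening and the end of the fourth injection.

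**3. Entry limit needed to absorb a given fall**

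The documents do not say how far counts may fall, so the relative fall f is an assumption. A patient who enters at level L and falls by f reaches L × (1 − f). To stay at or above the Section 2.5 limit, L must be at least limit ÷ (1 − f).

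| Assumed fall f | Platelets, 30 ÷ (1 − f) | Neutrophils, 0.5 ÷ (1 − f) |
|---|---|---|
| 10% | 33.3 | 0.56 |
| 20% | 37.5 | 0.63 |
| 30% | 42.9 | 0.71 |
| 50% | 60.0 | 1.00 |

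**4. Effect of a Day 7 count**

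If it is read before the third injection, the third and fourth injections follow a post-baseline result. The number of injections that a scheduled count could still stop rises from 0 of 4 to 2 of 4. Extra tests: 200 participants × 1 = at most 200.

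**The case against.** The strongest reply is that nothing here is wrong. Section 2.4 treats the two figures as a contraindication to interferon, and using one contraindication limit both at entry and during treatment is coherent. That stands: the sections do not contradict each other, and nothing in the document requires a buffer.

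A reader might infer that patients can start treatment at a level the protocol itself flags. The text does not support this, because both rules apply only below the limits. Nor does crossing a limit mean automatic withdrawal: Section 2.5 also requires the researchers to find that risk outweighs benefit.

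The reply can also point to other safeguards. Section 2.4 excludes coagulation disorders, long-term immunosuppressant use and autoimmune disease, and lets researchers refuse a patient. Section 2.5 has separate routes out for adverse events and for researcher judgement, and adverse events are reviewed at Day 7. These reduce the risk. None of them sets a count or produces one, and the 11 hospitals could apply the discretionary ones differently.

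Finally, Table 1 may not list every safety test. Section 6 puts the ECG before and after treatment, yet Table 1 marks it only at screening. The two-point wording in Sections 6 and 8 also covers vital signs, which Table 1 collects at all six visits, so that wording alone does not rule out further tests. Unscheduled counts are not forbidden, and the full protocol may add some. This limits the point to what the article schedules, but no part of the article places a count between the first and fourth injections.

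**Conclusion.** The point holds as a low-priority patient-safety improvement. On the schedule shown, no planned count can trigger the Section 2.5 blood rule while injections remain, and the entry limits give a margin of 0 for both platelets and neutrophils.

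The number of patients affected cannot be calculated. The documents give neither the distribution of baseline counts nor the size of a treatment-related fall, so any probability that someone crosses a limit would be built on guesses. It is reasonable to expect very few, but that is a judgement.

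A reader might also infer that the missing count biases the efficacy result or that the trial is unsafe as designed. The documents support neither. The conclusion rests on the article alone and on reading the Section 2.5 limits as applying to either count.

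**What to change.** 1. **Table 1:** mark a blood count at Visit 2 (Day 7), with the result to be read before the third injection. State the same timing in Section 6.
2. **Section 2.4:** set the entry limits above those of Section 2.5. For example, exclude at platelets <60 × 10^9/L or neutrophils <1.0 × 10^9/L, which allows for an assumed 50% fall. The sponsor's safety experts should choose the final values from the fall they wish to allow for, and should check that the platelet limit is also acceptable for a foraminal puncture.

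The two changes do different work: the first makes a fall visible in time to act, and the second gives room for a fall before it matters.

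**Cost:** up to 200 extra routine blood counts, at a visit where vital signs and a physical examination are already done, and probably very few extra screen failures, using screening counts that are already collected. The primary outcomes and the sample size do not change.

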### Drop-out criteria

2.5

During this trial, subjects experiencing the following conditions will be considered as dropout cases, and the reason and date of dropout will be recorded in a case report form.

Self-administration of drugs that affects the trial.Occurrence of adverse events (AEs) or severe adverse events (SAEs), which makes it inadvisable to continue considering the subjects’ interests.Abnormal blood routine changes (platelets <30 × 10^9^/L, neutrophil count <0.5 × 10^9^/L) during the administration of intervertebral foramen injections, leading the researchers to determine that further participation would pose a greater risk than benefit to the subjects.A participant requests to withdraw consent.A participant is lost to follow-up.The researchers consider that further participation will be inappropriate.

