## Statistical analysis

8

An independent statistician will perform the full analysis set (FAS), per protocol set (PPS), and safety analysis set (SS). FAS is used to analyze data collected from patients randomized in the trial and treated at least once. PPS is performed in cases that complete all steps of the experimental protocol. SS is performed to analyze the data collected from subjects who receive at least one treatment and have a record of safety indicators. The number of cases in the SS will be determined as the denominator to calculate the incidence of AEs and SAEs.

Descriptive statistical results will be shown as mean ± standard deviation for continuous data, and as numbers and percentages for categorical data. Chi-square or Fisher’s exact tests shall be used for categorical data and independent t-tests or rank-sum tests for continuous data, depending on whether the data meet the normal distribution and homogeneity of variance. *p* < 0.05 will be considered to indicate a statistically significant difference.

For safety evaluation, the proportions of AEs and SAEs will be calculated using chi-square or Fisher’s exact tests. We will perform a paired t-test or rank-sum test to compare differences in vital signs and laboratory test results during the screening period and at the end of the intervention.

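### Section 2.5 classes stopping injections and self-medication as dropout, with no diary or visits provided for afterwards, which risks informative truncation of the primary relief-day count

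*Protocol article*

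**What the plan says.** Section 2.5 (Drop-out criteria) gives one list with one consequence: "subjects experiencing the following conditions will be considered as dropout cases, and the reason and date of dropout will be recorded". The list has six entries. The first is "Self-administration of drugs that affects the trial". The next two are an adverse event or serious adverse event that makes continuing inadvisable, and low platelets or neutrophils during the injection course together with a risk-benefit judgement by the researchers. The rest are withdrawn consent, loss to follow-up, and a general researcher judgement. The blood-count and general-judgement entries speak of participation in the trial, not of the injections.

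Section 5.1 makes duration of pain relief a primary outcome beside the VAS score. It is the number of days on which the relief rate is at least 25%, taken from a daily diary. Table 1 schedules visits up to Day 90 after treatment.

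Section 8 defines the main population: "FAS is used to analyze data collected from patients randomized in the trial and treated at least once". The per-protocol set keeps only those who complete every step.

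Section 2.2 allows for one kind of loss: "Assuming a loss to follow-up rate of 15%, the adjusted sample size should be 100".

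On analgesics, section 4.1 permits tramadol under a response condition and disallows taking it on one's own initiative. Section 4.2 permits it as rescue for pain the patient cannot withstand, recorded in a diary.

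**The concern.** Only two of the six conditions, withdrawn consent and loss to follow-up, end observation by their nature. The other four describe patients who can still fill in a diary and attend visits. If a site follows section 2.5 as written, it closes these patients at the dropout date, and nothing else in the article tells it to go on collecting.

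This matters for two reasons. First, some triggers may depend on the assigned treatment. Section 6 names granulocytopenia and thrombocytopenia among the possible treatment-related reactions, and section 2.5 uses low neutrophils and platelets as a trigger. Self-medication for pain is plausibly more common in whichever arm relieves pain less. Second, the relief-day outcome has no denominator. A patient observed for two weeks cannot reach the count of one observed for three months, whatever the pain did afterwards. Days that were never recorded cannot be recovered by any later analysis plan, so the protocol has to settle this point.

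**Working it through.** **The plan's own figure.** Section 2.2 states that "the response rate was 46% in the treatment group and 23% in the control group", and for alpha "0.05 (bilateral) and power = 0.90, PASS17 software suggested that at least 85 subjects should be included in each group". With the unpooled normal approximation:

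n = (1.960 + 1.282)² × (0.46×0.54 + 0.23×0.77) / 0.23² = 10.51 × 0.4255 / 0.0529 = 84.5, so 85 per arm.

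85 / (1 − 0.15) = 100 per arm. Both figures reproduce; the sample size is not in error.

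**What the 15% covers.** It is labelled loss to follow-up, which is one of six dropout conditions. If the other conditions also cost data and total loss reached 20% or 25% (assumed), 80 or 75 per arm would remain. Power by the same formula would be about 0.88 or 0.86, for the responder comparison on which the trial was sized, not for the day count.

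**Sorting the six conditions.**

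| Condition in section 2.5 | Ends observation by nature? | Could depend on treatment? |
|---|---|---|
| Self-administered drugs that affect the trial | No | Plausibly, through pain |
| Adverse event making continuing inadvisable | No | Plausibly |
| Low platelets or neutrophils | No | Plausibly (section 6) |
| Researcher judgement | No | Possibly |
| Withdrawn consent | Yes | Possibly |
| Lost to follow-up | Yes | Possibly |

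**Illustration.** None of the following inputs is in the article except the visit schedule:

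- Window of 104 days: 14 treatment days plus 90, counting Day 90 from the end of treatment as Table 1 suggests.
- Share of days with relief, f: 0.45 on interferon, 0.30 on control.
- Proportion q in each arm drops out at Day 14.
- Days after dropout count as no relief.

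Expected days per patient = f × [(1 − q) × 104 + q × 14] = f × (104 − 90q).

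| q interferon / control | Interferon | Control | Difference | Change |
|---|---|---|---|---|
| 0 / 0 | 0.45×104 = 46.80 | 0.30×104 = 31.20 | 15.6 | none |
| 15% / 15% | 0.45×90.5 = 40.73 | 0.30×90.5 = 27.15 | 13.6 | −13% |
| 20% / 10% | 0.45×86 = 38.70 | 0.30×95 = 28.50 | 10.2 | −35% |
| 10% / 20% | 0.45×95 = 42.75 | 0.30×86 = 25.80 | 17.0 | +9% |

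**Sensitivity to the assumptions.**

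- Section 2.1 can be read as three months from enrolment. A 90-day window replaces the bracket by 90 − 76q, and the four differences become 13.5, 11.8, 8.9 and 14.6.
- With no true effect (f = 0.35 in both arms, 104 days), the spurious difference is −90 × 0.35 × (q interferon − q control). For 20% against 10% that is about −3 days, for 25% against 5% it is −6.3, with the sign reversed when the rates are reversed. Equal rates give zero.
- With f = 0.46 and 0.23, the true difference is 23.9 days. Dropout of 20% / 10% at Day 14 gives 17.7, 10% / 20% leaves it at 23.9, and 5% / 25% gives 27.0.

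So the error can go either way or vanish, depending on rates that the article does not give.

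**The case against.** The strongest reply is that section 2.5 never says that the diary or visits stop. It says that a reason and a date are recorded. A journal article may leave procedures after discontinuation to the full protocol, and the handling of missing diary days to the analysis plan. This stands in part: the end of data collection is the natural reading of dropout in a text about participation, but it is an inference. What remains is that the printed rule gives treatment stopping and study exit the same status, and a site needs them kept apart.

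Other stronger readings are tempting and are not supported:

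- That any adverse event or any other drug makes a patient a dropout. Both triggers are qualified, and tramadol, antipyretics and stable drugs for other diseases are permitted.
- That truncation is unequal between arms, or runs against interferon. No rates by arm are given, and the two plausible mechanisms pull in opposite directions. Table 1 also schedules laboratory tests only at screening and at Day 14, after the fourth injection, so the blood-count trigger may seldom act in mid-course.
- That the full analysis set removes dropouts or by its definition breaks the randomised comparison. It keeps everyone randomised and treated at least once.
- That missing days are scored as no relief. Section 5.1 is silent on this; the illustration assumes it.

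The illustration also has limits. It treats all dropout as recoverable, whereas true loss to follow-up is not. It gives dropouts the same relief rate as completers; patients who self-medicate for pain would probably have fewer relief days to lose. Finally, whether relief days after a disallowed drug should count is a choice of estimand, not an error to correct.

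**Conclusion.** The point holds as a risk built into the protocol text. Section 2.5 merges stopping injections and self-medication with leaving the study, and provides for no outcome collection afterwards. Applied as written, it would lose diary days for reasons that may depend on treatment, in a primary outcome that is a raw count of days.

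The size and direction cannot be determined from the article. The drop from 15.6 to 10.2 days and the rise to 17.0 show only what moderate imbalance could do under the assumed relief shares, Day 14 dropout and no-relief scoring. They are not estimates for this trial. The change is worth making because it is cheap now and the data cannot be recovered later.

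**What to change.** Split section 2.5 into two categories.

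1. **Stops study injections, or deviates from the protocol:** an adverse event making continuing inadvisable, low counts, researcher decision, self-administered drugs that affect the trial. Record the reason and date. These patients continue the daily diary and the scheduled visits, including Visits 4 to 6 up to Day 90, unless they withdraw consent, and their later data belong to the full analysis set.
2. **Leaves the study:** withdrawn consent and loss to follow-up. Only these end data collection.

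The clinical rules for stopping injections are not touched. Sections 2.5, 4.1 and 4.2 must be reconciled so that a site can tell which tramadol use makes a patient a deviation case and which is permitted; this review does not say which rule is right. How relief days after disallowed medication are counted, and how days still missing are handled, can be left to the analysis plan once the data are being collected.

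The cost is protocol wording, plus diary keeping and visits already scheduled for what should be a small number of patients. The sample size stays at 100 per arm, and the 15% allowance then lies closer to its label, with withdrawn consent as the only other exit.
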